### Preterm Child – Treated

All infants will receive parenteral and enteral nutrition according to clinical practice and routines.

The group of infants randomized to treatment with enteral Formulaid™ will receive AA and DHA with a quotient that is 2:1. The time period for the enteral supplementation will start during the first day of life until 40 weeks postmenstrual age. The dose given will be 100 mg AA/kg/day and 50 mg DHA/kg/day, i.e. with volumes ranging from 0.1 ml to 1 ml/day (see Appendix A for details in dosing).

### Preterm Child - Conventional fatty acid supplementation

A preterm child that is randomized to conventional treatment receives Clinoleic (with Vitalipid infant and Soluvit supplementation) according to regular clinical practice and routines as described below.

For all preterm infants the parenteral nutrition with glucose, amino acids and lipids is introduced within the first 24 hours of life. The infusion of lipid emulsion (Clinoleic 20%) is gradually increased during the first days of life to a maximum of 3,5g/kg/24 h at day 3 to 5 of life. Consequently, a preterm infant with a birth weight of 1 kg will receive a maximum of 15 ml lipid emulsion/24 h (3 g/kg) which, according to Brans et al (45) is within acceptable levels (i.e 2-3 g/kg/day) for Very low birth weight (VLBW) infants. Enteral feeding with human breast milk is introduced from the first day of life. According to our clinical practice we start with 1-5 ml/kg every third hour depending of maturity and birth weight. The amount of breast milk is slowly and carefully gradually increased during the first 7 to 10 days of life until the infant is fully enteral fed. With increasing enteral amounts the parenteral dose of lipid emulsion is decreased. Some of the most immature infants may have problems to tolerate increased enteral feeding leading to a longer period of parenteral feeding in low doses.

In conclusion, feeding VLBW infants according to clinical practice and routine are a regiment with *partial* parenteral nutrition combined with enteral nutrition.

If an infant does not tolerate any enteral feeding (for example gut problems as NEC or during any kind of surgery) give Formulaid™ before giving back the retention and flush the probe with little air afterwards. It is up to the responsible clinician to determine if Formulaid™ can be administered to the individual child.

### 6.3 Blinding

This is a randomized study with blinded ophthalmologic assessment of ROP stage. Retinal examination will be performed approximately once weekly starting at four to five weeks of age according to a standardized protocol and to clinical screening praxis. The evaluation of ROP occurs independently from the study and pediatric ophthalmologists will be unaware of which infants are participating in the study.

## 7 STUDY CONDUCT

### 7.1 Ethics and Regulatory Considerations

This study will be conducted in accordance with current Good Clinical Practices (GCPs) and International Conference on Harmonization (ICH) recommendations, as well as all applicable local, state, and federal regulations and guidelines regarding the conduct of clinical trials.

### 7.2 Independent Ethics Committee

The protocol, informed consent form, and other written subject information must be submitted to the “Regionala Etikprövningsnämnden i Göteborg” (EPN) [www.epn.se](http://www.epn.se) and their written unconditional approval must be obtained prior to commencement of the study.

Verification of unconditional approval from EPN of the protocol and the approved informed consent form will be forwarded to DSM, the manufacturer of the study medication, prior to shipment of study medication supplies to the site.

### 7.3 Informed Consent/Assent Form

Informed consent by the parents/guardians for each subject will be obtained before initiating any study procedures. Both parents/guardians will have to sign the informed consent. Informed consent should be obtained as soon as possible after birth and no later than 36 hours after birth. One copy of the signed and personally dated informed consent must be given to each parent/guardian and one signed and personally dated copy must be retained in the investigator's trial records. The “Declaration of Helsinki” recommends that consent be obtained from each potential subject or parents/guardians in biomedical research trials after the physician has explained to the individual the purpose, methods, anticipated benefits, and potential hazards of the trial and discomfort it may entail.

Potential subject's parents/guardians should also be informed of their right not to participate or to withdraw from the study at any time. If the individual is in a dependent

relationship to the physician or gives consent under duress, an independent physician should obtain the informed consent. If the individual is legally incompetent (i.e., a minor or mentally incompetent), informed consent must be obtained from the parents, legal guardians, or legal representative in accordance with the law in Sweden. See the “Declaration of Helsinki”.

If a protocol amendment substantially alters the study design or there is an increase of a potential risk to the subject:

- the informed consent form or subject information sheet must be revised and submitted to EPN for review and approval; and
- the approved revised form must be signed by parents/guardians to subject currently enrolled in the study; or
- the new form must be used to obtain consent from new parents/guardians prior to enrollment into the study.

#### **7.4 Subject Data Protection**

The Investigator is responsible for keeping a list of all subjects (who have been allocated subject numbers) including subject numbers, full names (of parents/guardians and child, if applicable) and parents addresses.

The parents/guardians should also be informed in writing and agree to the possibility of audits and /or monitoring by authorized representatives of the Sponsor, the manufacturer of the study drug, and/or regulatory authorities in which case a review of those parts of the laboratory records relevant to the study may be required.

The parents/guardians should be informed in writing and agree to that the results will be stored and analyzed in a computer, maintaining confidentiality in accordance with the Swedish Personal Data Ordinance (1998:1191). “Personuppgiftslagen” (PUL SFS 1998:204, SFS 1998:1191)

#### **7.5 Biobank**

Samples taken in this study will be stored in a biobank according to the National Swedish Board of Health and Welfare in accordance with the Biobanks in Medical Care Act (2002:297) The biobank is registered at the national board of health and welfare in Sweden (Socialstyrelsen). The parents/guardians will be informed about this.

### **8 STUDY EVALUATIONS**

#### **8.1 Efficacy evaluations**

All values obtained from efficacy evaluations should be recorded onto the electronic case record form (eCRF). Serum samples will be taken simultaneously with clinical blood sampling.

### **Fatty acid analyses**

The analyses of fatty acids will be performed at the University of Gothenburg, where the method has been developed and validated on the limited volumes available in pre-term infants. Total lipids of serum will be extracted according to Folch et al. (46). Serum lipids will be fractionated on a single SEP-PAK aminopropyl cartridge (Waters Corp., Massachusetts, USA) and phospholipids eluted with methanol after washing with chloroform:isopropanol 2:1 and 2% HAc in ether. The phospholipid fraction will be transmethylated in methanolic-HCL-3N at 80°C for 4 hours. The method has been described earlier (47). The fatty acid methyl esters will be separated by capillary gas-liquid chromatography in an Agilent gas chromatograph, *supplied by* Department of Biological and Environmental Sciences, University of Gothenburg. The separation will be recorded with Agilent GC-MS Chem Station software and the data analyzed using Agilent MassHunter software. The fatty acid methyl esters will be identified by comparison with retention times and mass spectra of pure reference substances (Sigma Aldrich Sweden AB, Stockholm, Sweden and Larodan AB, Solna, Sweden).

### **ROP examination**

The retinal examination will be performed once weekly starting at five to six weeks of age but not earlier than at postmenstrual age of 31 weeks, according to a standardized protocol and to clinical screening praxis. The ophthalmologic assessment will be performed with strict criteria according to general Swedish Guidelines issued by the Swedish Ophthalmological Society: The Guidelines are available at following link: [www.swedeye.org/SOTA/rop/SOTA-ROP\\_2006.pdf](http://www.swedeye.org/SOTA/rop/SOTA-ROP_2006.pdf).

### **Growth**

Length, weight and head circumference will be registered weekly from birth until 40 weeks postmenstrual age and at 2.0 y corrected age and at 5,5 y uncorrected age.

### **Body Composition (Lund and Gothenburg)**

Peapod will be performed at postmenstrual age at 40 weeks followed by DXA at 2.0 y corrected age and at 5,5 y uncorrected age

### **Brain/Neurologic development**

Cranial ultrasound will be performed postnatal days 3 and 7 and once between days 21-35 and once between postnatal weeks 32-40. MRI and DTI of the brain will be performed at 40 weeks PMA.

At 2.0 y corrected age a clinical examination including neurologic evaluation (neurologist) cognitive evaluation with BaileyIII-test (psychologist) will be performed and at 2.5 years an ophthalmologic examination will be performed.

At 5.5 years a clinical examination including neurologic evaluation (neurologist) cognitive evaluation with WPPSI-IV and behavioral questionnaire SDQ, short visuo-

motor test will be performed. Extensive ophthalmologic examination, including visual perception and morphologic and functional examination of the retina, will be performed at 6.5 years.

Morbidities BPD, IVH, PDA, NEC will be assessed at 40 weeks PMA according to the SNQ register.

## 8.2 Safety Evaluations

All values obtained from safety evaluations should be recorded onto the CRF. Safety evaluations consist of the following:

- **AE reporting:** include SAEs and AEs related to the study drug shall be recorded starting from receiving informed consent until the final study examination / sampling. AE reporting is further outlined in section 9, Safety.
- **Physical examination:** A complete physical examination will be performed in all subjects at birth according to standard clinical routines.
- **Vital signs:** Heart rate, blood pressure, pO2 and breath frequency will be monitored at birth and recorded in the eCRF in VIEDOC. Followed by registration of HR and MABP in excel every second hour up to day 7 PMA. Subjects are connected with continuous surveillance of heart beat, breath frequency and pO2. An alarm will notify the personnel and if any true divergences have occurred, these will be recorded in the patient record. Children with artery catheter are always under continuous intra artery blood pressure control with alarm for any irregular episodes
- Samples of ventricular & tracheal aspirate: At postnatal day 1 gastric fluid will be taken by the insertion of a feeding tube early after birth and analysed for composition e.g.inflammatory and oxidative biomarkers and fatty acids. Tracheal aspirate will be obtained during routine endotracheal suctioning daily in infants treated on ventilator and analysed for composition e.g. inflammatory and oxidative biomarkers and fatty acid composition.
- Retinal exam: Retinal exam will be performed according to clinical screening protocol. Any deviations from normal will be described in the CRF. RetCam images shall be taken if doable at each screening examination and has at least to be taken prior to treatment of severe ROP.
- Cranial/Cerebral ultrasound will be performed in all subjects by an experienced neonatologist or a pediatric radiologist as clinical routine. Any deviations from normal will be described in the CRF.
- **Cardiac Ultrasound - PDA** will be performed in all subjects by an experienced neonatologist or a pediatric cardiologist as clinical routine prior to PDA treatment. If the baby has not been treated for PDA, ultrasound will be performed day 3 and day 7.
- The following variables will be registered in the CRF;
  1. Width of ductus: xx mm
  2. Dominating direction of the shunt through DA: left-right/equilibrium/right-left

- 729 3. Speed of DA shunt: yy m/sec
- 730 4. La/Ao quotient:
- 731 5. Reversed diastolic flow in post-ductorial aorta: yes / no
- 732 • **Magnetic resonance imaging of the brain** will be performed in all subjects by a pe-
- 733 diatric radiologist as clinical routine. Any deviations from normal will be described in
- 734 the CRF.
- 735 • **Laboratory evaluations:** Laboratory assessments will be performed according to
- 736 standard clinical routines. Blood samples for fatty acid analyses; 2 ml from cord
- 737 blood and 0.6 ml from the child will be taken according to present clinical practice at
- 738 0h, 72h, d7, d14, every other week until PMA 29w, and then at PMA 30w, 32w, 34w,
- 739 36w, and 40 weeks. Breast milk samples are taken day 7 and postmenstrual weeks 32
- 740 and 40. Length, weight and head circumference are measured weekly to a PMA of 40
- 741 weeks.
- 742 Analyses of triglycerides cannot be taken more frequently then described in the pro-
- 743 tocol as the small circulating blood volume of these very preterm infants will not al-
- 744 low more sampling than what is already specified in the protocol.
- 745 It is extremely rare in our neonatal intensive care unit that a WLBW infant is planned
- 746 to receive more than 3 g fat/kg/24 h intravenously, but if it should happen the infant is
- 747 always very thoroughly followed by clinical checkups with daily measurements of
- 748 plasma triglycerides and blood gases (as a safety control of metabolic state).
- 749 ***Laboratory evaluations consist of:***
- 750 **Chemistry:** Total and conjugated bilirubin at days 7, 14 and at postnatal weeks 32
- 751 and 40.
- 752 **Plasma glucose:** Blood for measurement of p-glucose is obtained from routine blood
- 753 gas measurements (taken prior to feeding) and will be recorded in the CRF through-
- 754 out the study.
- 755
- 756 **8.3 Other Evaluations**
- 757 • **Maternal and perinatal history:** Maternal and perinatal history will be recorded as
- 758 soon as possible after birth after questioning the subject's parents and/or recorded
- 759 from the mother's patient record for the pregnancy.
- 760
- 761 • **Maternal dietary habits**
- 762
- 763 A questionnaire regarding maternal dietary habits will be performed after birth at day 7
- 764 to retrospectively register eating habits during pregnancy and at 40 weeks PMA to reg-
- 765 ister dietary habits during postnatal care.
- 766
- 767 • **"Patient/parent" involvement**
- 768
- 769 A validated questionnaire "Parent's concerns about participating in this clinical trial" on
- 770 preterm infants will be used to collect data at the beginning, and at the end of the clini-
- 771 cal trial period. In addition, a parent's focus group will form and meet twice a year to
- 772 discuss a family-centered approach to clinical research. Research questions include: (1)
- 773 The perceived challenges of being involved in a clinical trial; (2) The perceived ad-

vantages of being involved in a clinical trial; and (3) The experiences of patients at different points in the clinical trial to improve interaction and joint decision making in the present study. We will start a "patientråd" in which a number of preterm patient associations (including EFCNI-www.efcni.org) are invited to one meeting/year during which improvements in care and clinical studies in preterm infants will be discussed.

- **Care at Retcam examination (Sthlm ,Lund & Gothenburg)**

A questionnaire regarding parent's experience of Retcam examination and the baby's wellbeing during and after the examination, will be performed at the first Retcam examination. We also want to correlate the answers to the baby's medical records. Different nursing care techniques will be compared and correlated to the baby's wellbeing to find the most optimal care.

- **Examination of the intestinal flora**

When the child is 3-5 days, 14 days, 28 days, and at discharge from the neonatal department, but not later than PMA 34 weeks, feces will be collected. At the same time four sterile cotton swabs will be rotated in the oral cavity of the infant. The feces and the cotton swabs will be sent for microbiological analyzes to study the early pattern of the normal intestinal. This is done to map the child's early normal bacterial flora and if the flora is affected by the intake of Formulaid™.

## **9 SAFETY**

### **9.1 Recording Adverse Events**

Adverse events related to study drug must be recorded starting from the time of informed consent until the final study examination / sampling day. Any medical condition present at the initial study day (birth day), which remains unchanged or improves, should not be recorded as an adverse event at subsequent examination / sampling days. However, if there is **deterioration** of a medical condition that was present at the initial study day (birth, day 0), this should be considered a **new** adverse event and reported. This information is collected by examining the subject. Ongoing adverse events at the final study day should be followed until the event is resolved or remains stable.

Clinically significant changes (abnormalities), in the judgment of the investigator, in physical examination from the baseline exam will be recorded as an adverse event.

The following information must be collected and recorded for each AE:

- AE term (diagnosis)
- Action taken regarding AE
- AE outcome (resolved, ongoing, death, or lost to follow-up)
- AE causality (not related, possibly related, related)

The investigator should determine study drug relationship for each adverse event. AEs occurring prior to administration of the study drug will be considered as not related to the study drug. The Investigator will be using the following explanations for assessment of causality:

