## 6.2 Study Drug Administration and Dosing

Regarding fatty acid supplementation to preterm infants the today's regime at all neonatal intensive care units in Sweden is to prepare a mixture of Vitalipid infant and Soluvit with Clinoleic. In addition, according to today's clinical praxis and pharmacy regimes the preparation of Clinoleic, Vitalipid infant and Soluvit lasts for seven days if stored at +4 to +6 and prepared by the local pharmacy. Infants randomized to Formulaid™ will additional to Clinoleic receive 0,1-1ml daily administered *enteral as an oral drug*. Start of administration will start on the first day of life (within 24 hours) preferably after the first enteral feeding in association with the second feeding. If the infant of some clinical reason cannot receive Formulaid™ within the first 24 hours this should be reported as an AE.

Formulaid™ (100 mL) will be thawed overnight in refrigerator and then left to reach room temperature before being allocated to oral syringes.

One mL oral syringes with cap will be filled with Formulaid™ and then stored in -80 degrees C at each responsible clinic.

At inclusion of an infant the number of study ID marked syringes needed throughout the study period will be allocated. These will be stored in refrigerator at the ward or at home.

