**9.2 Reporting Serious Adverse Events**

A serious adverse event (SAE) related to the study drug is defined as any adverse drug experience occurring at any dose that results in any of the following outcomes:

- Results in death,
- Is life-threatening (NOTE: The term "life-threatening" in the definition of "serious" refers to an event in which the subject was at risk of death at the time of the event; it does not refer to an event which hypothetically might have caused death if it was more severe).
- Results in inpatient hospitalization or prolongation of existing hospitalization,
- Results in a persistent or significant disability/incapacity, or
- Results in a congenital anomaly/birth defect.

Important medical events that may not result in death, be life-threatening, or require hospitalization may be considered a serious adverse drug experience when, based upon appropriate medical judgment, the event may jeopardize the subject and may require medical or surgical intervention to prevent one of the outcomes listed in this definition.

Any SAE occurring during the study (from receiving informed consent until end of study) or within 30 days after study completion will be reported to the Sponsor within 24 hours of knowledge of the event.

In the event of an SAE, the SAE/DSM form available in the electronic Trial Master File (TMF) is to be completed and reported to UBC Geneva by fax ([contact] or [contact]) within 24 hours of learning about the event regardless of whether all information is known. An e-mail will also be sent to [[contact]](mailto:[contact]) to inform about the SAE.

Initial SAE reporting can be done by telephone with written reports to follow by fax within 24 hours.

All SAEs must be followed until resolution (subject has returned to baseline status of health), or until stabilization (the investigator does not expect any further improvement or worsening of the reported event).

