### 3.2.2 Secondary Efficacy Variables

Following secondary efficacy variables will be analysed:

- Postnatal serum fatty acid (in mol%) composition in preterm infants with and without AA:DHA supplementation (at 0h, 72h, day 7, day 14, every second week until PMA of 29 weeks and thereafter at 30, 32, 34, 36, 40 weeks PMA). Missing data will not be imputed, analysis will be performed using Mixed Models for Repeated Measures (MMRM) where missing data at random is assumed.
- Outcome of neonatal morbidities (reported as Adverse Events [AE] from birth to 40 weeks PMA)
  - BPD – this morbidity is evaluated at 36 weeks PMA and will be analysed including the complete ITT population with deaths considered as non-events but their follow-up time will contribute to the total follow-up in the analyses of event rate performed by Poisson regression. Sensitivity analysis of BPD will be performed handling all deaths as endpoint also beside confirmed BPD. Drop-out due to other reasons will be considered as non-event.
  - IVH grade 0-4 – this morbidity is evaluated at an early stage post-birth, and larger amount of missing data is not expected. Drop-outs with missing IVH will be handled as non-events. Sensitivity analysis of IVH will be performed handling all deaths with missing IVH as worst value of this endpoint (?). Drop-out due to other reasons will be considered as non-event. Analyses will be performed using Mantel-Haenszel Chi-square test.
  - PDA - this morbidity is evaluated at an early stage post-birth, and larger amount of missing data is not expected. Drop-outs with missing PDA will be handled as non-events. Sensitivity analysis of PDA will be performed handling all deaths with missing PDA as event (?). Drop-out due to other

|                                     |  |                                    |               |
|-------------------------------------|--|------------------------------------|---------------|
| STATISTISKA KONSULTGRUPPEN   |  | Statistical Analysis Plan          |               |
| Protocol:
Mega Donna Mega |  | Protocol No:
MEGADONNAMEGA 16-7 |               |
|                                     |  | Version:
1.0                    | Page 14 of 21 |

reasons will be considered as non-event. Analyses will be performed using Fisher's Exact test.

- NEC – this morbidity will be analysed in the same way as the primary variable, using Poisson regression in the main and survival analysis in the sensitivity analysis.

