### 3.3.2 Adverse Events

Significant AEs are collected from birth onwards during the study, as per the table below. AEs specified event and category are available for the summaries.

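### The protocol ties AE recording to a study drug that only one arm receives, while the SAP compares all AEs between arms and takes morbidities from AE reports

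*Combined protocol and SAP*

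**What the plan says.** **Recording duty (protocol).** Section 9.1: "Adverse events related to study drug must be recorded starting from the time of informed consent". In section 8.2, AE reporting is to "include SAEs and AEs related to the study drug shall be recorded starting from receiving informed consent", which can be read as drug-related events only, or as all SAEs plus drug-related AEs. Section 9.2 begins with a definition: "A serious adverse event (SAE) related to the study drug is defined as any adverse drug experience occurring at any dose".

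**Protocol text pointing the other way.** The fields that 9.1 requires for each AE include "AE causality (not related, possibly related, related", so unrelated events are foreseen. Section 9.1 also makes clinically significant examination changes, and worsening of a condition present at birth, into AEs with no condition on cause. Section 9.2 requires prompt reporting of "Any SAE occurring during the study (from receiving informed consent until end of study".

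**SAP.** Section 3.3.2: "Significant AEs are collected from birth onwards during the study, as per the table below". The table has no causality filter. Section 4.7.2 tabulates all AEs, SAEs and AEs by causality. A note appended to the SAP extends the safety population to every randomised infant.

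**Source of the morbidities.** SAP 3.2.2 describes them as "Outcome of neonatal morbidities (reported as Adverse Events [AE] from birth to 40 weeks PMA" and then lists BPD, IVH, PDA and NEC. Protocol 8.1 (Brain/Neurologic development) assesses the same four at 40 weeks PMA from the SNQ register.

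**Late first dose.** Protocol 6.2: "If the infant of some clinical reason cannot receive Formulaid™ within the first 24 hours this should be reported as an AE". Protocol 7.3 allows consent up to 36 hours after birth.

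**The concern.** A between-arm AE comparison needs the same events to be recordable in both arms. A duty limited to drug-related events does not provide that here. The control arm has no study drug, and the definitions of possibly related and related in 9.1 turn on timing from, or response to, the drug. A control infant can hardly qualify. Under protocol section 4 the treating nurse or doctor receives the allocation, so the people who judge relatedness know the arm.

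The error could run in either direction. Events could be missed in controls because there is no drug to relate them to, or a harm in the supplement arm could be left off the AE form because it was judged unrelated. Since the safety population is all randomised infants, both arms appear side by side in the AE tables, where a difference in recording would look like a treatment effect.

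More is at stake if AE forms also supply the morbidities. BPD and IVH are the fourth and fifth tests in the SAP's confirmatory sequence (section 4.1), and arm-dependent recording there would be outcome misclassification by arm. The primary outcome is not touched: it comes from blinded retinal examinations.

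**Working it through.** The documents give no AE rate or recording rate, so there is no stated figure to reproduce. The check sets the passages side by side and then illustrates size on assumed inputs.

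**1. The two instructions.**
- Which events: drug-related (9.1 recording sentence; 9.2 definition) against any cause (9.1 causality field and examination rule; 9.2 reporting rule; SAP 3.3.2 and 4.7.2).
- From when: consent, up to 36 hours after birth (protocol 8.2, 9.1, 7.3), against birth (SAP 3.2.2, 3.3.2).
- For whom: the SAP notes include all randomised infants, so a comparison of arms is intended.

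SAP section 6 reports no changes from the protocol, so the mismatch is not acknowledged.

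**2. Exposure by outcome.**
- *AE and SAE totals:* the AE form is the only source. Exposed.
- *Treatment-related rows:* near zero in controls by construction, so they carry no between-arm information.
- *Sepsis:* a secondary aim in both documents, but absent from the register sentence in protocol 8.1 and from the SAP 3.2.2 list. In the SAP it appears as data only in the AE table. Exposed.
- *NEC:* has the register, but no scheduled examination like the ultrasounds. Exposed if AE forms are used.
- *IVH and PDA:* have the register, plus cranial and cardiac ultrasound in all subjects (protocol 8.2). Exposed only if AE forms are used. The SAP's AE table also shows no mapping of its haemorrhage entries to the 0–4 grade that is tested.
- *BPD:* has the register, and the Note-to-SAP of 14 April 2020 defines it as oxygen need at 36 weeks PMA, which involves no relatedness judgement. That note names no data source. Exposed only if AE forms are used.

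**3. Size, as an illustration.** Assume equal true event rates p in both arms, full recording in the supplement arm and a fraction a recorded in controls. The values of p and a are assumptions; n = 105 per arm is the plan's.

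Apparent RR = p / (a·p) = 1/a.

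Chance of a significant false excess in the supplement arm at two-sided 5%, with d = p − a·p and p̄ the mean of the two recorded rates:

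Φ{ [d − 1.96·√(2p̄(1−p̄)/n)] / √([p(1−p) + ap(1−ap)]/n) }

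For p = 0.20 and a = 0.50: d = 0.10 and p̄ = 0.15. The first standard error is √(2×0.15×0.85/105) = 0.0493, and 1.96 times it is 0.0966. The second is √((0.16+0.09)/105) = 0.0488. The result is Φ(0.07) = 0.53.

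| Control events recorded | Apparent RR | False excess, p = 20% | False excess, p = 40% |
|---|---|---|---|
| 90% | 1.11 | 6% | 9% |
| 75% | 1.33 | 16% | 33% |
| 50% | 2.0 | 53% | 89% |
| 25% | 4.0 | 91% | above 99% |

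With full recording in both arms the formula gives Φ(−1.96) = 2.5%.

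**4. Late first dose.** Only a supplement infant can generate this AE. Each such infant with no other AE adds 1/105 = 0.95 percentage points to that arm's any-AE row. It is a separate term and leaves the morbidity counts unchanged.

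**The case against.** The strongest reply is that protocol section 9, read whole, does not restrict recording. It asks for a causality grade that includes unrelated events, counts pre-dose events as unrelated rather than excluding them, makes examination changes AEs whatever their cause, and requires any SAE to be reported. The SAP then lists events to be collected from birth with no filter. The four main morbidities have a register, and three of them also have scheduled examinations or an objective criterion in both arms.

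Much of this stands, and it rules out three stronger readings.
- A reader might infer from the one sentence in 9.1 that controls should have no AEs at all. The rest of section 9 contradicts that, and nothing shows that sites worked that way.
- A reader might infer that neither safety nor the morbidities can be fairly compared, or that a NEC case judged unrelated is lost. NEC is a listed AE, a register morbidity and an SAP endpoint in both arms, and the other three also have the register. The bias there depends on the source used.
- A reader might infer that consent at 24 to 36 hours followed by allocation to supplement creates an AE by itself. Section 6.2 requires a clinical reason, and late consent alone is not stated to be one.

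What does not stand is that the other sentences cure the restrictive one. They leave two incompatible instructions, with unblinded staff choosing between them. Nor does the register sentence settle the source: the SAP, which governs the analysis, names AE reports.

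**Conclusion.** The concern holds as an unresolved conflict with real potential for bias. Where the restrictive wording was followed, AE recording depended on arm; the documents do not establish that it was followed. The effect would be greatest for AE totals and sepsis. Treatment-related rows cannot be compared between arms in any case. For BPD, IVH, PDA and NEC, arm-dependent misclassification is possible only if AE forms feed the analysis, as SAP 3.2.2 says and protocol 8.1 does not. The late-first-dose AE is one-sided but limited to AE totals.

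The apparent relative risks of about 1.1 to 4.0 rest on assumed control-arm recording of 90% to 25%, full recording in the supplement arm and equal true rates. They show how sensitive the comparison is and do not estimate what happened.

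**What to change.** 1. Amend protocol 8.2, 9.1 and 9.2 so that all AEs and SAEs are recorded in both arms from the same start time whatever the cause, with causality graded afterwards, and align SAP 3.3.2 with that start. The SAP is dated 19 November 2019 and the protocol planned its last subject's completion for 1 September 2018, so collection may already be over. In that case, disclose how AEs were actually recorded in each arm and limit the between-arm AE conclusions accordingly.
2. Change SAP 3.2.2 so that BPD, IVH, PDA and NEC come from the SNQ register or the scheduled examinations in both arms, not from AE forms. Name the source for sepsis.
3. Report late-first-dose entries separately from the between-arm AE comparison. The 24-hour first-dose passage (protocol 6.2) and the 36-hour consent passage (protocol 7.3) must be reconciled.

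The cost is a short protocol amendment, some SAP wording and somewhat more AE entry in the control arm. If collection is complete, the cost is deriving the morbidities from the register or examination data and a plain statement of how AEs were recorded; an amendment is unlikely to recover events that were never entered.
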